## 2.0 OBJECTIVES AND SCIENTIFIC AIMS

- Aim 1: To determine the comparative effectiveness of virtual MT versus virtual CBT for anxiety and co-morbid symptoms in cancer survivors.
  - Hypothesis 1(a): MT will be non-inferior to CBT for treating anxiety symptoms among survivors at week 8 (end of treatment) and week 26 (long-term follow-up).
  - Hypothesis 1(b): Compared with CBT, MT will be associated with significantly greater improvement in fatigue co-occurring with anxiety.
  - Exploratory Hypothesis: Survivors may have unique experiences with MT and CBT for anxiety during cancer survivorship.
- Aim 2: To identify patient-level factors associated with greater anxiety symptom reduction for MT and CBT.
  - Hypothesis 2: Specific socio-demographic characteristics (e.g. age, sex, race, education) or psychological attributes (i.e. expectancy) will be associated with treatment response to MT or CBT.

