### 14.2 Statistical Analyses.

We describe the analysis for each aim below using the intention-to-treat (ITT) principle (i.e. participants will be analyzed according to their randomly assigned treatment group regardless of drop-out or treatment adherence status). For all specific aims, our main analytic tool will be linear mixed-effects models (LMMs) because our primary outcome (anxiety) and secondary outcomes (e.g. fatigue, insomnia) are repeated continuous outcomes over time. This statistical procedure takes into account within-subject correlations from repeated measurements in the same subjects and allows estimation of between-group differences without necessitating exclusion of participants with missing data. The general template of each LMM will model the outcome as a function of treatment arm and assessment time (categorical), controlling for the randomization stratification variables (baseline anxiety medication use, preferred language, study site), and including a subject-specific random intercept. We will tailor this general LMM template to test the specific aim hypotheses by adding interaction terms (e.g. time-by-intervention) and additional covariates of interest to the model, and by reparametrizing the assessment time variable to focus on specific contrasts.

**Aim 1 – Hypotheses 1(a) and 1(b):** We will plot the outcome measure trajectories by randomization arm over time and summarize each outcome measure at each assessment time by treatment arm using descriptive statistics. Comparisons between randomization arms with respect to changes in symptom outcomes will be based on specific coefficients from time-by-arm interactions added to the general LMM template described above. Specifically, the model will include all time points (categorical) at which the outcome was assessed (baseline, week 4, 8, 16, 26), and the time-by-arm interaction will include multiple coefficients corresponding to the time-by-arm interaction at each discrete post-baseline time point. Our

[figure not shown]

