statistical inferences, however, will focus on the interaction coefficients at 8 and 26 weeks, which are interpreted as the differences between arms in change from baseline to 8 and 26 weeks, respectively. For Hypothesis 1(a), our two primary endpoints are HADS anxiety score changes at 8 weeks and 26 weeks. Based on the LMM coefficients for the time-by-arm interaction at week 8 and week 26, we will perform two tests of whether MT is non-inferior to CBT at reducing HADS Anxiety within a non-inferiority margin of 0.35 SD for both comparisons. Non-inferiority of MT to CBT will be tested at significance threshold of  $p < 0.025$  for each comparison, controlling the overall Type I error at 0.05 for our primary endpoint comparisons. For Hypothesis 1(b), we will use a similar LMM evaluating BFI scores over time to test whether the MT arm had significantly greater improvement in fatigue (BFI score) compared to the CBT arm at weeks 8 and 26. In contrast to our primary endpoint non-inferiority comparisons, these tests will be superiority tests. For the other co-morbid symptoms (e.g. depression, insomnia) and quality of life, we will compare the arms using the same methods described for Hypothesis 1(b). Given that a small number of cancer survivors may experience recurrence of disease during the 26-week study, we will conduct sensitivity analyses, excluding those individuals who experienced a recurrence during the study period. Our sensitivity analyses will not replace the primary analysis.

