**Aim 2 – Heterogeneity of Treatment Effect (HTE):** An essential part of patient-centered care is recognizing that not all patients will respond to treatments the same way. We will conduct exploratory, hypothesis-generating HTE analyses to identify patient-level factors associated with treatment response to either MT or CBT by incorporating six relevant variables (i.e. sex, race, ethnicity, education, outcome expectancy, and time since cancer diagnosis) and variable-by-intervention interaction terms in our mixed-effects model described above. For these five exploratory LMM-based analyses, we will guard against inflated Type I error due to multiple testing by adjusting the variable-by-intervention interaction p-values for the false discovery rate. We recognize that this type of subgroup analysis, although patient-centered, may need to be interpreted with caution and cannot replace the primary analyses. We intend to approach the evaluation of HTE based on existing literature and patient/clinician input. Our current focus on evaluating and reporting HTE will be based on the approach proposed by Kent et al. However, recognizing other factors may also contribute to treatment responses, we will apply promising emerging Bayesian and machine learning methods, which can identify HTE and subgroups based on multiple variables simultaneously and are potentially more powerful than traditional univariate methods.

**Qualitative Analyses:** All interviews will be transcribed verbatim and imported into NVivo Pro version 12.0 for analysis. The semi-structured interviews will be analyzed using theoretical thematic analysis procedures per guidelines by Braun and Clarke. Such analysis is aimed at identifying patterns driven by an *a priori* theoretical framework or research questions. Themes will be identified using a semantic approach in which themes are derived from “the explicit meaning of the data and the analyst is not looking for anything beyond what a participant has said.” Two coders will independently code each interview

[figure not shown]

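### As worded, Aim 2 tests effect modification averaged over five visits, baseline included, rather than modification of change at weeks 8 and 26, and its count of tests is inconsistent

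*Protocol*

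**What the plan says.** Protocol section 2.0 states Aim 2 as finding patient factors linked to a larger reduction in anxiety under each therapy. Hypothesis 2 refers to "Specific socio-demographic characteristics (e.g. age, sex, race, education) or psychological attributes (i.e. expectancy").

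The model comes from section 14.2. The general template is a linear mixed model "including a subject-specific random intercept". For Aim 1, "the model will include all time points (categorical) at which the outcome was assessed (baseline, week 4, 8, 16, 26"), so baseline is a response and not a covariate. The effect of arm on change sits in the time-by-arm coefficients, which are "interpreted as the differences between arms in change from baseline to 8 and 26 weeks, respectively".

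The Aim 2 paragraph of section 14.2 then proposes "incorporating six relevant variables (i.e. sex, race, ethnicity, education, outcome expectancy, and time since cancer diagnosis"). What it adds for each of these is described as "variable-by-intervention interaction terms in our mixed-effects model described above". The next sentence reads "For these five exploratory LMM-based analyses, we will guard against inflated Type I error", to be done by "adjusting the variable-by-intervention interaction p-values for the false discovery rate".

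Two other places bear on this. Section 14.2 says in general terms that the template will be tailored for each aim by adding interactions and recoding time. Section 11.3 and Table 1 have expectancy (METE) collected at week 0 and again at week 8.

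**The concern.** By the protocol's own logic, a difference between arms in change is a time-by-arm coefficient. Modification of that difference is therefore a variable-by-arm-by-time coefficient. The Aim 2 paragraph names a term without time, and names it twice, the second time as the quantity whose p-value is adjusted. Followed literally, it mixes in the baseline visit, where randomisation makes modification zero in expectation, and weights all visits alike.

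At stake are the size and meaning of the reported modification, which section 7.0 says should inform personalised decisions. The FDR step also needs a known number of tests, and the paragraph gives two: six variables, then five analyses. In addition, expectancy measured at week 8 comes after randomisation and can itself be affected by treatment, and the paragraph does not say which measurement is the modifier.

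**Working it through.** **The plan's own figure.** No power is stated for Aim 2. The one power figure in section 14.2 (80%; 150 per arm, 15% attrition, margin 0.35 SD, one-sided 0.025) reproduces. With 150 × 0.85 = 127.5 per arm, power = Φ(0.35/√(2/127.5) − 1.96) = Φ(0.835) = 79.8%.

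**1. What the two-way coefficient estimates.** Take the model with categorical time, arm, time-by-arm, variable, variable-by-arm and a random intercept. The variable-by-arm term does not change over time and the covariance is exchangeable. With complete data its estimate is therefore a contrast of subject means over the five visits:

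E(two-way) = (δ0 + δ4 + δ8 + δ16 + δ26)/5, with δ0 = 0 by randomisation.

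The table assumes a full modification of 2.0 HADS points. The ratios do not depend on that value or on the correlation.

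| Modification at weeks 0, 4, 8, 16, 26 | Two-way expectation | Share of the 2.0 points |
|---|---|---|
| 0, 2, 2, 2, 2 (constant) | 8/5 = 1.6 | 80% |
| 0, 1, 2, 2, 2 (half at week 4) | 7/5 = 1.4 | 70% |
| 0, 1, 2, 1, 0 (peak at week 8) | 4/5 = 0.8 | 40% |
| 0, 0, 0, 1, 2 (late) | 3/5 = 0.6 | 30% |

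The three-way coefficients at weeks 8 and 26 recover the value at each week. A check with 60 simulated trials, 15% dropout and a true effect of 2.0 gave 1.47 (Monte Carlo SE 0.08) for the two-way term. The three-way terms gave 1.89 at week 8 and 1.97 at week 26 (SE 0.13 each).

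**2. Precision.** Inputs: N = 300 and SD 4.2 from section 14.2; assumed are a balanced binary modifier (75 per cell), complete data and within-person correlation r.

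- Var(two-way) = 4 × 4.2² × [r + (1 − r)/5]/75
- Var(three-way at one week) = 4 × 4.2² × 2(1 − r)/75

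For the half-at-week-4 pattern, the information of the two-way test relative to a single-week three-way test is 0.7² × 2(1 − r)/[r + (1 − r)/5]:

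- r = 0.3: 0.686/0.44 = 1.56
- r = 0.5: 0.49/0.60 = 0.82
- r = 0.6: 0.392/0.68 = 0.58
- break-even: 0.98(1 − r) = 0.2 + 0.8r, so r ≈ 0.44

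Power for a constant 2.0-point modification (two-sided 0.05, before FDR):

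| r | Two-way | Three-way, one week |
|---|---|---|
| 0.3 | 70% | 41% |
| 0.5 | 57% | 54% |
| 0.7 | 47% | 76% |

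**3. The count.** The listed variables are sex, race, ethnicity, education, expectancy and time since diagnosis: six, in a closed list. The next sentence has five analyses. Age would make seven. At an assumed FDR level of 0.05 (none is stated), the smallest Benjamini-Hochberg cutoff is 0.05/5 = 0.010, 0.05/6 = 0.0083 or 0.05/7 = 0.0071. If weeks 8 and 26 are tested separately, six variables give 12 tests (0.0042) and seven give 14 (0.0036).

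**The case against.** The best defence is the tailoring sentence in section 14.2. It covers all aims and allows added interactions and a recoded time variable. Since the model's treatment effect already sits in the time-by-arm terms, the Aim 2 wording could be shorthand for interactions with that effect. If so, the attenuation disappears. The exact terms of an exploratory model may also be set out in an analysis plan not shown here. This stands in part: the sentence permits the right contrast. It does not specify it, however, and the Aim 2 paragraph does name a different term as the one tested. The point rests on that wording and not on silence.

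Three stronger readings are tempting and are not supported:

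- **That the two-way test always loses power, for example 42% of the information.** That figure is 1 − 0.58 at an assumed correlation of 0.6. Below about 0.44 the comparison reverses for the same pattern, and the protocol gives no correlation.
- **That a hypothesised modifier is left untested in breach of Hypothesis 2.** Age appears there only as an example, is collected at baseline (section 11.7), and could enter the Bayesian and machine-learning work planned for other factors. It is a mismatch to reconcile.
- **That chance baseline imbalance biases the result.** It adds noise, not expected bias.

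The analyses are also labelled exploratory and hypothesis-generating, to be read with caution.

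**Conclusion.** The point holds for the text as written. The named term estimates modification averaged over five visits, while the aim is modification of change. The estimate is 80% of the true effect if modification is constant after baseline and 70% if week 4 shows half. It is smaller if modification peaks at one week or builds late. These ratios assume complete data and the random-intercept model; they need no assumption about correlation or effect size. The effect on power can go either way and should not be claimed as a loss.

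Six against five is a plain contradiction in consecutive sentences and leaves the FDR family undefined. The absence of age is a lesser inconsistency. The sample size and the primary non-inferiority conclusion are unaffected.

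**What to change.** In the Aim 2 paragraph of section 14.2:

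1. State that each modifier is tested by the variable-by-arm-by-time contrasts at weeks 8 and 26, with variable-by-time and all lower-order terms in the model, preferably as one joint test per modifier.
2. State that expectancy is the week-0 METE score.
3. Reconcile six and five, and either add age to the list or drop it from Hypothesis 2.
4. State the FDR family size: 6, or 7 with age, under one joint test per modifier; 12 or 14 if each week is tested separately.

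The cost is wording, with no new data. The FDR family becomes larger than the stated five, and at low within-person correlation the single-week contrasts have less power than the two-way test.

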**Sample Size and Power:** Our sample size is based on our primary hypothesis that MT is non-inferior to CBT for anxiety reduction at week 8 and week 26. We will perform two tests of whether MT is non-inferior to CBT at reducing HADS Anxiety at week 8 and also at week 26, each with a non-inferiority margin of  $D=0.35$  SD for both comparisons. These comparisons will be based on LMM coefficients for the time-by-arm interaction at week 8 and week 26;

[figure not shown]

however, we present our power calculation based on two-sample t-tests of differences between the arms in their change scores. Therefore, our power estimate is conservative; that is, in our LMM-based analysis, we will have slightly higher power than presented below, with all other assumptions held constant. Assuming 150 participants are randomized to each arm, 15% attrition, and a one-sided significance threshold of 0.025 (controlling the overall Type I error at 0.05 for our two primary endpoint comparisons), we will have 80% power to find MT non-inferior to CBT with respect to week 8 and 26 HADS Anxiety scores within a non-inferiority margin of  $D=0.35$  SD. Justification of Non-inferiority Margin: A recent large study used multiple rigorous methods to empirically estimate a difference of 1.7 points as the MCID for the HADS scales. In preliminary data of CBT recipients with baseline HADS Anxiety scores  $\geq 8$ , the SD for the HADS Anxiety score was 4.2 at week 8 (end of treatment). Additionally, in a large, recently completed acupuncture trial of cancer survivors, among 159 patients with baseline HADS Anxiety scores  $\geq 8$ , the HADS Anxiety score SD was 4.0 during follow-up. Based on these studies, we assume our HADS Anxiety score SD will be approximately 4.2. Dividing the raw-score MCID of 1.7 points by 4.2 yields standardized difference (i.e. Cohen's D) of 0.40. Our non-inferiority margin of  $D=0.35$  SD is smaller than the HADS Anxiety standardized MCID ( $D=0.40$ ); as such, our non-inferiority margin and statistical approach will find MT to be non-inferior to CBT only if MT is not meaningfully worse than CBT. We confirmed with our patient advisory groups, using concrete examples, that the non-inferiority margin of  $D=0.35$  SD would not represent a meaningful difference between the treatments. Qualitative Analyses: The number of participants required to draw meaningful conclusions from semi-structured interviews is determined by saturation, i.e. the point at which existing themes are fully understood and no new themes emerge through further data collection. Prior research has indicated that thematic saturation can typically be obtained with fewer than 15 interview participants, although these findings were based on relatively homogenous samples. Given that we are seeking to capture perspectives from a diverse group of survivors, we will plan for 30 interviews in each treatment arm to achieve thematic saturation. We achieved saturation at  $N=30$  interviews in an ongoing qualitative study of our virtual integrative medicine program.

## 15.0 TOXICITIES/RISKS/SIDE EFFECTS

MT and CBT are non-pharmacological interventions. All potential risks that might occur as a result of participation will be detailed in an informed consent form and will also be fully discussed with each patient prior to enrollment. We will also explain to each patient that in the unlikely event of an injury directly resulting from the research procedures, every effort will be made to make the facilities and professional skills of MSK available to them.

Physical Risks: MT and CBT are not associated with any physical risks.

Psychological Risks: During MT and CBT sessions, cancer survivors may experience psychological discomfort when thinking about their experiences with cancer and how it has affected their lives. In addition, study assessments will consist of questions related to socio-demographics, medical history (including cancer type and treatment), anxiety, depression,

[figure not shown]

fatigue, insomnia, pain, cognitive difficulties, and health-related quality of life. It is possible that participants may feel uncomfortable with some of these questions. Although there is the potential for psychological distress while completing study questionnaires or participating in semi-structured interviews, this has been found to be a rare event in our previous and ongoing studies. CTCAE Version 5 will be utilized for side effect evaluation.

Financial and Legal Risks: There are no financial or legal risks to the study participants. All research interventions and evaluations are provided free of charge to study participants.

Privacy and/or Confidentiality Risks: There is a small risk of loss of privacy or confidentiality as someone could get access to the personal information in the study participants' study records.

### 15.1 Serious Adverse Event (SAE) Reporting

An adverse event is considered serious if it results in ANY of the following outcomes:

- Death
- A life-threatening adverse event
- An adverse event that results in inpatient hospitalization or prolongation of existing hospitalization
- A persistent or significant incapacity or substantial disruption of the ability to conduct normal life functions
- A congenital anomaly/birth defect
- Important Medical Events (IME) that may not result in death, be life threatening, or require hospitalization may be considered serious when, based upon medical judgment, they may jeopardize the patient or participant and may require medical or surgical intervention to prevent one of the outcomes listed in this definition
- *List any additional events that require SAE reporting (pregnancy, AEs of special interest (AESI), secondary malignancies, etc.)*

Note: Hospital admission for a planned procedure/disease treatment is not considered an SAE.

SAE reporting is required as soon as the participant starts investigational treatment/intervention. SAE reporting is required for 30 days after the participant's last investigational treatment/intervention. Any event that occurs after the 30-day period that is unexpected and at least possibly related to protocol treatment must be reported.

Please note: Any SAE that occurs prior to the start of investigational treatment/intervention and is related to a screening test or procedure (e.g., a screening biopsy) must be reported.

All SAEs must be submitted in PIMS. If an SAE requires submission to the HRPP Office per [IRB SOP RR-408 'Reporting of Serious Adverse Events.'](#) the SAE report must be submitted

[figure not shown]

within 5 calendar days of the event. All other SAEs must be submitted within 30 calendar days of the event.

The report should contain the following information:

- The date the adverse event occurred
- The adverse event
- The grade of the event
- Relationship of the adverse event to the treatment(s)
- If the AE was expected
- Detailed text that includes the following
  - An explanation of how the AE was handled
  - A description of the participant's condition
  - Indication if the participant remains on the study
- If an amendment will need to be made to the protocol and/or consent form
- If the SAE is an Unanticipated Problem

## 16.0 PROTECTION OF HUMAN PARTICIPANTS

Voluntary Nature of the Study: All study participants will provide informed consent prior to enrolling. The participant will be informed of the procedures to be followed, alternatives, potential benefits, side effects, risks, and discomforts. We will inform patients that they are free to withdraw from the study at any time and that their participation is voluntary.

Payments to Participants: Participants will receive \$40 after completing the questionnaire at week 8 and \$60 after completing the questionnaire at week 26.

Protection Against Risk: The PI has led two NIH-funded trials of major depressive disorder and generalized anxiety disorder. He has both clinical and research experience in mental health diagnosis and treatment. During study assessments, our well-trained research staff will be readily available by phone/email/videoconference to assist patients as needed, and our qualitative methods specialist has extensive experience in conducting interviews on potentially sensitive topics in a safe and appropriate manner. If a research team member observes a study participant displaying elevated psychological distress, they will inform the study clinicians so that they can evaluate and potentially refer the patient to MSK's psychiatry services, if clinically warranted. In addition, all study therapists must undergo a standardized training process and meet a rigorous certification standard before delivering any treatments to research participants. All therapists are specifically trained to build rapport, develop a psychotherapeutic relationship, and establish a supportive context. Treatment fidelity is routinely monitored and audited to ensure that therapists are following the protocol and adhering to safety procedures. Every effort will be made to ensure the safety and comfort of the study subjects. The therapists will monitor the patients for adverse events during each session, and report any potential AEs to the PI. In the unlikely event of significant

[figure not shown]

psychological distress, we will refer participants for urgent evaluation by MSK's Psychiatry Service. If a patient displays active suicidal ideation and poses a significant and acute risk of self-harm, we will contact the patient immediately to connect the patient with emergency psychiatric assessment and care.

Alternative Treatment: The alternative to participating in the study is to receive other non-pharmacologic interventions (e.g. other forms of psychotherapy besides CBT) or pharmacologic agents (e.g. anxiolytics, antidepressants). During the informed consent process, potential study subjects will be informed that these alternative treatments are available, that their participation in the study is entirely voluntary, and that their care will not be affected in any way if they decide not to participate in the study.

Risk/Benefits Ratio: With the American cancer survivor population expected to exceed 22 million by 2030, there is a pressing need to address anxiety, an exceedingly common long-term consequence of cancer, in this growing population. The COVID-19 pandemic has not only exacerbated psychological distress, but also highlighted many of the pre-existing barriers to mental health resources and services. If successful, our proposed research on virtually delivered MT and CBT has potential to address some of these barriers and allow more patients to access evidence-based interventions for anxiety. The risks to subjects are small in comparison to the valuable and timely scientific information and potential clinical benefits that will result from the conduct of this study.

